### Pressure pain thresholds

2.4.

PPTs are the minimum pressure stimulus perceived as painful and have been used to evaluate pain processing alterations (45)*.* PPTs will be assessed using a portable digital pressure algometer (WAGNER FORCE TEN FDX, United States) with a tip of one square centimeter. All measures will be performed by a single assessor trained to exert a pressure of 0.50 kgf/s (46). Participants will be positioned lying supine on a padded table. The algometer tip will be placed perpendicular to the skin at two points: (i) the center of the patella (local hyperalgesia), and (ii) the lesser tubercle of the humerus of the contralateral shoulder (widespread hyperalgesia) (46) (Supplementary Figure S1). Participants will be asked to report when the pressure sensation becomes painful (46). PPTs will be assessed twice at each site with a 30 s interval between assessments, and the mean will be used for statistical analysis. This protocol has been reported to have good intra-rater reliability in individuals with PFP (ICC = .72 to.80; SEM = .41 to.55 kgf/s; MDC = 1.14 to 1.52 kgf/s) (47).

### Physical performance

2.5.

The Single Leg Hop Test and Forward Step-Down Test will be obtained as measures of physical function. Prior to testing, three familiarization trials will be performed to minimize learning effects. To perform the Single Leg Hop Test, participants will be positioned standing on the tested leg, with the non-tested knee flexed at 90° and the arms crossed behind their back. They will be asked to hop forward as far as possible, landing on the same leg while maintaining their balance (14, 15) (Supplementary Figure S2). The distance between the initial and final heel positions will be recorded in centimeters with a measuring tape. If participants lose their balance or swing their arms, the trial will not be considered valid and will be repeated (14, 15). The mean of three valid repetitions will be used for statistical analysis. Reliability of this test has been reported to be excellent (ICC = .96; SEM = 4.56 cm) (48). For the Forward Step-Down Test, participants will be positioned standing with their test leg on a step, their hands on their waist, and their non-test leg in front of the step with the knee extended and the ankle dorsiflexed. The step height will be standardized so that all participants achieve 60° of knee flexion during testing (49). Participants will be asked to tap the floor with their non-test heel and then return to the starting position (15) (Supplementary Figure S3). Participants will be asked to perform as many repetitions as possible in 30 seconds and the number of repetitions will be recorded (15). Repetitions where the participant does not tap the floor, loses their balance, or change the position of their hands will not be considered valid and will not be added to final test score (15). The Forward Step-Down Test will be performed once without interruptions. Reliability of this test has been reported to be excellent (ICC = .94; SEM = .53 repetition) (50).

### Trunk muscle endurance

2.6.

Anterior and lateral trunk endurance will be assessed with the Prone-Bridge and Side-Bridge tests, respectively. For the Prone-Bridge test, participants will be initially positioned lying prone on an exercise mat, propped on their forearms and feet, with shoulders and elbows flexed at 90°. Arms will be shoulder-width apart and feet will be hip-width apart (15). Participants will be asked to raise the pelvis from the floor, maintaining this static position as long as possible (15) (Supplementary Figure S4). For the Side-Bridge test, participants will be positioned side-lying on an exercise mat, with their hips in a neutral position, legs extended and both feet in tandem on the exercise mat. The foot on the side being tested will be positioned behind the contralateral foot, in a staggered position. The support arm will be placed vertically with the elbow aligned with the shoulder, and the contralateral hand placed on the waist (15). Participants will be asked to lift their hips off the mat, and to hold the static position as long as possible (15) (Supplementary Figure S5). Both tests will be stopped when participants no longer sustain the test position and the duration in seconds will be recorded (15). Verbal encouragement will be not provided during the test, although one verbal correction might be given to correct participants’ positioning if necessary. Reliability of these tests has been reported to be excellent (ICC = .91 to.96; SEM = 4.79 to 5.46 s; MDC = 13.28 to 15.13 s) (51).

### Biomechanics

2.7.

Kinematics and kinetics data during single leg squat, step-down and single leg hop tasks will be collected using a 5-camera motion analysis system at 100 Hz (VICON Motion Systems, United Kingdom) synchronized with a force plate at 4000 Hz (4060; BERTEC, United States). Retroreflective markers (14 mm) will be placed according to the Plug-in-Gait model, with one additional maker on the medial knee (Supplementary Figure S6). Upon marker placement, a standing calibration trial will be performed, and the knee joint center will be determined using a virtual Knee Alignment Device (KAD) to minimize *cross-talk* errors. Participants will be then instructed to perform three practice trials of each task for familiarization. For the single leg squat task, participants will be asked to stand with their tested leg on the force plate and the non-tested knee flexed at 90°. They will be instructed to squat to an angle greater than 60° of knee flexion, and then to return to the initial position (Supplementary Figure S7). The step-down task will be performed similarly to the Forward Step-Down Test except that it will be performed on the force plate and without instructions to perform as many repetitions as possible (Supplementary Figure S8). Five trials of the single leg squat and step-down tasks will be obtained. For the single leg hop task, participants will stand on the force plate, with their hands on the waist. Participants will be instructed to hop forward as far as possible with their test leg, landing on the same leg (propulsion phase, Supplementary Figure S9). The same procedure will be then performed with the participant landing on the force plate (landing phase, Supplementary Figure S10). Three trials of each phase will be obtained, six in total.

### Muscle function

2.8.

Maximal torque, RTD and force steadiness will be collected with an isokinetic dynamometer with an acquisition frequency of 100 Hz (System 4 Pro; Biodex, United States). The starting muscle group (hip abductors or knee extensors/flexors) and the type of contraction (isometric, concentric or eccentric) will be randomized.

For the assessment of the knee extensors/flexors, participants will be seated with their hips and non-tested knee flexed at 90°. The dynamometer axis will be aligned with the center of the knee joint. Two belts crossing the trunk, one around the pelvis, and another on the distal tested thigh will be used to stabilize the participants (13, 14) (Supplementary Figure S11). The isometric torque will be tested at 60° of knee flexion, while concentric and eccentric torques will be tested from 20° to 90° of knee flexion with an angular velocity of 30°/seconds (13, 14). For the hip abductors assessment, the participants will be positioned in a side-lying position with the test leg on top of the non-test leg and, hips in neutral sagittal and transverse plane positions. The dynamometer axis will be aligned to the anterior superior iliac spine at the level of the greater trochanter (13). Four belts will be used to stabilize non-test leg and the trunk (Supplementary Figure S12). The isometric torque will be tested at 30° of hip abduction and concentric and eccentric torques will be tested from 0° to 30° of hip abduction with an angular velocity of 30°/seconds (13).

Maximal torque and RTD will be assessed as follows. For the isometric contraction familiarization, two submaximal contractions of six seconds will be performed, with one-minute interval between them (13, 14). Afterwards, two maximal contractions of six seconds will be collected, with a three-minute interval between them (13, 14). For concentric and eccentric contraction familiarization, five submaximal contractions and two maximal contractions will be performed with one-minute interval between them (13, 14). Then, three maximal contractions of six seconds will be collected, with a three-minute interval among them (13, 14). Participants will be verbally encouraged to perform maximal contractions and visual feedback exhibiting torque-time curve will be provided (13).

Force steadiness will be assessed during sub-maximal isometric force-matching tasks. The target torque will correspond to 10% of maximal torque estimated from the isometric test (12, 52). The dynamometer monitor will display the targeted torque simultaneously with the torque generated by the participant. Participants will be instructed to match their generated torque with the target torque and keep it as steady as possible. Two familiarization trials of 10 seconds will be performed, with a 30 s interval between them (12, 52). Then, three trials of 20 seconds, with one-minute interval among them will be collected (12, 52).

### Data analysis

2.9.

A Woltring filter with a two mean square error will be applied to reduce the vibratory noise that could arise during the marker trajectories due to soft tissue artefact marker trajectory in Vicon Nexus (2.12; VICON Motion Systems, United Kingdom). Vertical ground reaction force (VGRF) will be filtered at 10 Hz using a zero-lag fourth-order low-pass filter. For single leg squat and step-down tasks, the beginning of the task will be defined as the moment when the participant starts performing the descent phase of the task (measured *via* the increase in knee flexion of the tested limb), while the end of the task will be defined as the moment when the participant returned to double leg stance (52). For single leg hop task, landing phase will be defined from initial contact (instant when VGRF first exceeds 10N) to peak knee flexion, while propulsion phase will be defined from peak knee flexion to take off (instant when VGRF first decreases below 10N). Hip, knee, and ankle joint kinematics will be calculated using a joint coordinate system approach, while trunk and pelvis kinematics will be calculated relative to the laboratory coordinate system. Peak and range of motion of trunk, pelvis, hip, knee and ankle kinematics in the sagittal and frontal planes will be calculated. Net joint moments will be also computed using standard Newton-Euler inverse-dynamics equations and will be expressed as internal moments normalized to each participant’s body mass (53). PFJ contact force and stress will be also calculated based on a previously described biomechanical model proposed by Devita and Hortobagyi (54). In this model, hip, knee and ankle joint angles and moments are used to calculate hamstrings, quadriceps and gastrocnemius muscle force. In doing so, the knee extensor moment is adjusted by the co-contraction of the knee flexors (55) (Figure 2). PFJ stress will be then calculated for the entire task, but the peak value will be the variable of interest.

**Figure 2 F2:**
[figure not shown]
Flowchart of the PFJ model.

Maximal isometric, concentric and eccentric torques will be determined as the highest value obtained during each contraction type and will be normalized by the body mass of each participant ([N·m·kg^−1^] × 100) (17, 52). RTD will be calculated by dividing normalized torque variation by the time variation (ms) from the onset of the contraction up to 30% and 60% of maximal torques (17, 52). Contraction onset will be defined as the point at which the torque curve exceeded the baseline value by 2% of maximal torque (17, 52). Force steadiness will be determined by the coefficient of variation of torque for each trial (torque standard deviation/mean torque × 100) and the mean of the 3 trials will be used for statistical analysis (12, 52). The first and last 3 seconds of contraction will not be considered for analysis (12, 52). A custom-written code in MATLAB will be used to obtain all variables of interest (R2017a; The MathWorks, Inc, United States).

### Statistical analysis

2.10.

Descriptive statistics (mean, median, standard deviation, and interquartile intervals) will be calculated for all variables of interest. Generalized Linear Mixed Model (GLMM) will be used to investigate group-by-time differences. The type of matrix will be chosen according to the Akaike Information Criterion (AIC) in order to assess the adherence index of the model (56). The lower the AIC, the higher the adherence (56). Group and time interaction effects will be considered fixed, while participant effects will be considered random. Pairwise comparisons will be performed with Bonferroni *post hoc* tests when significant interactions or main effects are determined. Mean differences [95% confidence intervals (CI)] and effect sizes (Cohen’s *d* [95% CI]) for each *post hoc* comparison will be calculated. The guidelines for interpreting the Cohen’s *d* are: 0 to 0.40 small effect, 0.41 to 0.70 moderate effect, 0.71 or large effect (57). Statistical significance level will be set at .05.

For the first stage of the regression analyses, univariate linear regression models will be used to determine to what extent changes in each biomechanical, muscle function, pain processing and psychological features are associated with changes in self-reported pain, physical performance measures, self-reported function, HRQOL and physical activity level in individuals with PFP. A significance level of *p* ≤ .10 rather than the conventional level of *p* < .05 will be used to ensure that the univariate analyses are sufficiently sensitive to identify potential prognostic factors for entry in the model (58). For the second stage, all potential prognostic factors that showed significant associations on univariate analyses will be entered into a stepwise multivariate linear regression with backward elimination (*p* ≤ .10) in order to identify a group of factors that are independently associated with the clinical outcomes. For the final multivariate models, the significance will be set at .01 to minimize the results being adversely influenced by the likelihood of increased risk of Type I error associated with multiple analyses. The predictive power of each final model will be determined by calculation of the percentage of explained variance (adjusted *R*^2^).

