### Participants

2.1.

Participants aged 18 to 40 years were recruited through advertisements at social media, universities, gyms and public parks and divided in two groups: individuals with PFP (*n* = 144) and control individuals without PFP (*n* = 85). The following inclusion criteria were considered for PFP group (29): (i) Insidious symptoms of PFP lasting at least three months, (ii) worst knee pain in the last month of at least 20 mm on a 0–100 mm Visual Analogue Pain Scale (VAS), (iii) symptoms of PFP during activities that load patellofemoral joint (e.g., squatting, running, jumping, prolonged sitting, stair negotiation). To be included in the control group, participants had no signs or symptoms of PFP or other neurological or lower limb musculoskeletal conditions. Exclusion criteria for both groups were history of: patellar subluxation, surgery in any lower limb joint, trauma or injury at the knee, or ligament instability. Additional exclusion criteria for the follow-up assessments are: (i) occurrence of knee trauma or injury (both groups); (ii) development of knee pain (only for control group); (iii) development of other medical conditions that may influence the findings (both groups). Participants’ baseline demographics are presented in Table 1.

**Table 1 T1:** Participants’ demographics at baseline.

Variables	PFP group (*n* = 144) Mean ± SD	Control group (*n* = 85) Mean ± SD
Females (*n*)	108	64
Males (*n*)	36	21
Age (years)	23 ± 5	22 ± 3
Height (cm)	166 ± 8	165 ± 9
Body mass (kg)	68 ± 14	62 ± 13
BMI (kg/cm^2^)	25 ± 4	23 ± 4

Abbreviations: SD, standard deviation; PFP, patellofemoral pain; BMI, body mass index.

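### The mixed model has no term for sex, a recorded and balanced variable, so PFP-control mean differences may have wider intervals than necessary; the group-by-time test is practically unaffected

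*Protocol article*

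**What the plan says.** Section 2.10 of the protocol article states the purpose of the model: "Generalized Linear Mixed Model (GLMM) will be used to investigate group-by-time differences". It then gives the terms: "Group and time interaction effects will be considered fixed, while participant effects will be considered random". I read this as group, time and their interaction as fixed effects, plus a random participant effect. No covariate is named.

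Between-group contrasts are among the stated outputs. Post hoc tests follow an interaction or a main effect: "Pairwise comparisons will be performed with Bonferroni *post hoc* tests when significant interactions or main effects are determined". For these the article promises "Mean differences [95% confidence intervals (CI)] and effect sizes (Cohen’s *d* [95% CI]) for each *post hoc* comparison will be calculated".

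Table 1 in section 2.1 records sex by group. The row for women reads "Females (*n*) 108 64", that is 108 of 144 with PFP and 64 of 85 controls.

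**The concern.** Hop distance, step-down repetitions, trunk hold times, strength and joint mechanics could plausibly differ between men and women. If they do, a model without sex leaves that difference in the variance between participants. This variance enters the standard error of every comparison between different people: the PFP-control difference at each visit, and the group main effect that can trigger the post hoc tests. Balance on sex protects the estimate from confounding but does not recover the precision.

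Baseline assessment is complete, so precision cannot be gained by recruiting more participants. A variable already collected is the cheap way to gain it.

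**Working it through.** The article gives no sample-size, power or interval-width figure, so there is none to reproduce.

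**Inputs from the article (Table 1).** PFP: 108 women + 36 men = 144. Controls: 64 women + 21 men = 85. Shares of women: 108/144 = 75.0% and 64/85 = 75.3%. Overall 172/229 = 75.1%.

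**Assumptions.** The within-sex SD of an outcome at one visit is set to 1. The male-female gap *d* is taken as 0.3, 0.5, 1.0 or 1.5 of these SDs. Outcomes are treated as roughly normal with an identity link.

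**Confounding.** The shift in the PFP-control difference from omitting sex is (36/144 − 21/85) × *d* = 0.0029 × *d*. At *d* = 1.5 this is 0.0044 SD, which is negligible.

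**Precision at one visit.** With p = 0.751, p(1 − p) = 0.187.
- Share of variance due to sex: R² = 0.187*d*² / (1 + 0.187*d*²).
- Equivalent number of participants: 229 / (1 − R²).
- Half-width with sex in the model: 1.96 × √(1/144 + 1/85) = 1.96 × 0.1368 = 0.268.
- Half-width without sex: the same multiplied by the square root of the pooled variance. At *d* = 1.0 the pooled variance is [143 + 84 + 144(0.25)(0.75) + 85(21/85)(64/85)] / 227 = (227 + 27.0 + 15.8) / 227 = 1.189, so the half-width is 0.268 × 1.090 = 0.292.

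| Assumed gap (SD) | R² | Half-width without sex | With sex | Narrower by | Equivalent n |
|---|---|---|---|---|---|
| 0.3 | 1.7% | 0.270 | 0.268 | 0.8% | 233 |
| 0.5 | 4.5% | 0.274 | 0.268 | 2.3% | 240 |
| 1.0 | 15.8% | 0.292 | 0.268 | 8.3% | 272 |
| 1.5 | 29.6% | 0.320 | 0.268 | 16.2% | 325 |

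The shortcut 1 − √(1 − R²) gives 2.3%, 8.2% and 16.1% for the last three rows.

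**Check in the mixed model.** Random-intercept models were simulated with and without sex, with an assumed within-person correlation of 0.7 and 40 runs per setting. With complete pairs, the visit-specific intervals narrowed by 2.4%, 8.3% and 16.7% at gaps of 0.5, 1.0 and 1.5. With 30% loss at follow-up, the follow-up figures were 1.8%, 7.0% and 14.3%.

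**Interaction and within-group change.** A constant sex effect cancels in follow-up minus baseline. In the simulation at *d* = 1.0 with complete pairs, the standard error of the interaction was 0.105 with and without sex. With 30% loss it narrowed by less than 1% at every gap.

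**Outcome scales.** Section 2.9 divides torque and joint moments by body mass, derives rate of torque development from the normalized torque, and expresses steadiness relative to the participant's own mean torque. Hop distance is in centimetres (2.5) and trunk holds are in seconds (2.6), without scaling to body size. The upper rows of the table are therefore the likelier ones for the normalized outcomes.

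**The case against.** The strongest objection is that the model's declared target gains nothing. Hypothesis 1 concerns change within the PFP group. Hypothesis 2 predicts that gaps from controls widen by follow-up, which is the group-by-time interaction. This stands. A reader might infer that the test of hypothesis 2 loses power, but the cancellation shown in the working rules that out.

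A second objection is that nothing stated is invalid and that a condensed article may leave covariates to a fuller plan. The first part stands: this is a matter of efficiency, and a reader who infers bias from the omission would be wrong, given the balance in Table 1. The second part stands only partly, because the article does set out its model terms and sex is not among them.

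Third, the gain is wholly assumed, and body-mass scaling may shrink it. This also stands, and is why a range is given.

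Three further steps may tempt a reader: adding sex for the pain, psychological and quality-of-life scores as well, adding sex-by-time, or arguing that sex protects against unequal loss of men and women. The article gives no sex differences for those scores, no sign that change differs by sex, and no retention figures. None of the three is supported.

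Last, a sex term is not quite free of side effects. If Cohen's *d* were standardized by the SD left after sex, it would rise without any change in the mean difference. At a gap of 1.0 SD the factor is √1.187 = 1.09, so 0.38 would become 0.41 and move from the article's small band to its moderate band. Fixing the standardizer removes this.

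**Conclusion.** The point holds as a modest one about precision. The PFP-control mean differences and the group main effect are stated outputs, and their intervals will be wider than necessary to whatever extent an outcome differs by sex. The narrowing available runs from negligible (0.8% at a gap of 0.3 SD) to about 16% (at 1.5 SD). Which value applies to which outcome cannot be learned from the article. The estimates are practically unbiased either way, and inference on change over time is practically unaffected. Minor weight.

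**What to change.** In section 2.10, add sex as a fixed effect to the mixed model for the performance, trunk endurance, muscle function and biomechanical outcomes, and report the PFP-control differences from that model. State that Cohen's *d* uses the SD not adjusted for sex, so that the 0.40 and 0.70 cut-offs keep their meaning. Sex-by-time is not required.

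The cost is one degree of freedom per model with 229 participants and a few words of text. No new data are needed. Follow-up is still under way, so the wording can be settled before the follow-up data are analysed.

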PFP is not self-limiting and is challenging to manage, with symptoms persisting for nearly two decades. Long-term pain is reported to continue in one of every two patients even after treatment (3, 23). Symptom severity may remain unchanged or increase in 50% of affected individuals (24, 25). As such, a similar prospective pattern would also be expected for physical and non-physical features given their previously reported cross-sectional association with PFP. Symptoms duration of individuals with PFP has been previously associated with biomechanical (26) and muscle function parameters (27), as well as pain itself (27, 28). However, the majority of the studies conducted to date have a cross-sectional or interventional design, which precludes the understanding of the natural history of these features in individuals with PFP.

Understanding changes over time in physical and non-physical features in individuals with PFP is a first step to gain knowledge regarding their evolution as part of PFP and its progression. In addition, investigating the prospective association of clinical outcomes (i.e., self-reported pain, physical performance measures, self-reported function, HRQOL and physical activity level) with physical and non-physical features may contribute to the identification of predictors of pain and disability in the long-term, as well as possible targets for interventions.

We have, therefore, designed a prospective longitudinal study aiming to investigate group-by-time changes over a minimum of 15 months in individuals with PFP, measuring their biomechanical, muscle function, pain processing, psychological features and clinical outcomes. In addition, we aim to investigate the extent to which changes in biomechanical, muscle function, pain processing, and psychological features are associated with changes in clinical outcomes. We hypothesize that: (1) individuals with PFP will present worse biomechanical, muscle function, pain processing, psychological features, and clinical outcomes at follow-up as compared to baseline; (2) potential differences in outcomes as compared to asymptomatic individuals at baseline will increase at follow-up; (3) changes over the time in biomechanical, muscle function, pain processing, and psychological features will be associated with changes in clinical outcomes; (4) there will be an association between changes over the time in biomechanical and psychological features.

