The investigation of the natural course of PFP can provide additional insights. For instance, PFJ stress has been suggested to play a central role in PFP pathophysiology (9). However, its behavior over time in individuals with PFP has never been investigated. As physical and non-physical features are thought to contribute to PFJ stress (9, 63–65), our study will be able to provide data regarding which features have associations with changes in PFJ stress in the long-term.

This study has some limitations that should be acknowledged. Only young adults were included in our study, limiting the generalizability of our findings to adolescents and older individuals. Our study will provide insights regarding the natural history of physical and non-physical features in individuals with PFP, however, cause and effect cannot be established given the study design. Lastly, this prospective study includes assessments in only two time points (i.e., baseline and follow-up). As PFP is characterized by intermittent symptoms (1), this may have an influence on the results.

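### Hypothesis 1, change within the PFP group, has no direct test or guaranteed confidence interval; it is reached only as a post hoc pair after another effect is significant

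*Protocol article*

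**What the plan says.** The Introduction states the first hypothesis as a directional contrast within one group: "individuals with PFP will present worse biomechanical, muscle function, pain processing, psychological features, and clinical outcomes at follow-up as compared to baseline". The second hypothesis is that differences from asymptomatic participants will widen by follow-up.

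The Statistical analysis section (2.10) fits a generalized linear mixed model per outcome: "Group and time interaction effects will be considered fixed, while participant effects will be considered random". Bonferroni pairwise comparisons follow only as "tests when significant interactions or main effects are determined". "Mean differences [95% confidence intervals (CI)] and effect sizes" are then promised for each of those post hoc comparisons. Descriptive statistics carry no such condition; they "will be calculated for all variables of interest". On the error level the section says "Statistical significance level will be set at .05".

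The section does not list the pairs to be compared or their number. It does not say whether a significant main effect leads to comparison of the four group-by-time cells or only of the marginal means.

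**The concern.** A hypothesis stated in advance should have its own contrast in the analysis. Here the within-PFP change is reached only through tests that answer other questions: whether the groups change differently, whether the two groups together change, or whether the groups differ on average. All three use the controls.

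Three things follow.

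- A real PFP change can go untested, so power for hypothesis 1 can only fall.
- For a true change, the estimates shown after the condition is met tend to be too large, because the condition favours large observed changes.
- An outcome that misses the condition has no promised interval for its change. The Introduction itself expects symptoms to stay the same or worsen in about half of those affected, so an interval that excludes material change would be a useful result.

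Hypothesis 2 has a related gap. The interaction tests it, but the between-group difference in change is a difference of two differences, not a pairwise comparison. No estimate or interval is promised for it even when the interaction is significant.

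**Working it through.** The protocol gives no sample size calculation, effect size or power, so there is no figure of its own to reproduce.

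**Inputs from the document**
- Group sizes at baseline: 144 with PFP and 85 controls (Participants).
- Two time points (Discussion).
- Significance level .05.

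**Assumptions (not in the document)**
- Two-sided tests and a normal approximation.
- All participants return.
- Equal SD of change in both groups; controls unchanged.
- Within-person correlation 0.5, so the SD of change, √(2(1 − 0.5)) = 1, equals the SD of the measurement.
- PFP change of 0.25 SD, with 0.15 SD as a smaller case.

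**Step 1. Direct test of the within-PFP change.** z = 0.25 × √144 = 3.00. Power = Φ(3.00 − 1.96) = Φ(1.04) = 0.85. At 0.15 SD, z = 1.80 and power = Φ(−0.16) = 0.44.

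**Step 2. The tests that must come first, at 0.25 SD.**
- Interaction: SE = √(1/144 + 1/85) = 0.137; z = 0.25/0.137 = 1.83; power = Φ(−0.13) = 0.45.
- Time main effect (average of the two group changes): effect 0.125, SE = 0.137/2 = 0.068; z = 1.83; power again 0.45.
- Group main effect (average over the two times): SE = √(0.75 × (1/144 + 1/85)) = 0.118. With no standing group difference the effect is 0.25/2 = 0.125, so z = 1.06. With a standing difference of 0.3 SD in the same direction it is 0.425, so z = 3.59 and the condition is almost always met.

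**Step 3. Power to reach and pass the within-PFP test, before Bonferroni.** These tests are correlated, so their joint behaviour was simulated for a change of 0.25 SD:

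| Route to the within-PFP comparison | Power |
|---|---|
| Unconditional | 0.85 |
| Interaction, time or group significant; no standing group difference | 0.73 |
| Same; groups differ by 0.3 SD or more | 0.84 to 0.85 |
| Interaction alone leads to the comparison | 0.43 |

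**Step 4. Bonferroni.** The number of pairs is not stated. As an illustration, four pairs give a critical value of 2.50 and power Φ(3.00 − 2.50) = 0.69 when the condition is always met. With no standing group difference, condition and four-pair correction together give about 0.64.

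**Step 5. Inflation of the reported change.** This is the mean PFP estimate when the written condition is met, divided by the true change. At 0.25 SD it is about 1.10 with no standing group difference and close to 1.00 when the groups differ by 0.3 SD or more. At 0.15 SD the corresponding range is about 1.34 down to 1.00 as the group difference grows.

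**Step 6. Retention.** The article gives no expected retention. At an assumed 70% (101 and 60), the unconditional power in step 1 becomes Φ(0.25 × √101 − 1.96) = Φ(0.55) = 0.71, so there would be less to spare.

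**The case against.** A reader might infer that the rule roughly halves power for hypothesis 1. The text does not support that as a general statement. The condition is met by a main effect as well as by an interaction, and the Discussion lists reported PFP impairments in kinematics, kinetics, strength, steadiness, psychological features and pain thresholds. Where the groups clearly differ, the group main effect meets the condition and costs almost nothing. Halving (0.85 to 0.43) requires that only the interaction lead to the within-PFP comparison. Such a reading is possible, because a main effect is often followed by marginal comparisons only, but the section does not say so.

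A reader might also infer that Bonferroni is shared over four or six pairs, some answering no hypothesis. No such family is stated; comparing time within each group would give one pair per group. Defining the family is detail that an article may leave to a fuller document.

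Nor do outcomes that miss the condition vanish. Their group means at each time are still described, which gives the point change. What is missing is the interval.

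Finally, an omnibus test followed by post hoc pairs is conventional, the controls are part of a group-by-time design, and the screen limits false positives across many outcomes. Removing all multiplicity correction would be debatable.

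These arguments reduce the size of the problem. They do not supply a test or interval for hypothesis 1 that stands regardless of other results, or an estimate for hypothesis 2.

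**Conclusion.** The point holds in a limited form. The section fixes a rule under which the study's first hypothesis is tested, and given an interval and effect size, only if another effect is significant; it promises no estimate for the second.

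Under the assumptions listed, and for a PFP change of 0.25 SD, the written condition lowers power from 0.85 to 0.73 at one end and by at most 0.01 at the other, depending on how far the groups differ. Bonferroni lowers it further by an amount that cannot be fixed from the text. Upward bias in the reported changes is about 0 to 10% at 0.25 SD and 0 to 34% at 0.15 SD. All of these figures depend on assumed effect sizes, correlation, control change and full retention.

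The loss of intervals for outcomes with little change does not depend on those assumptions and is the stronger reason to amend the plan.

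**What to change.** In the Statistical analysis section, name two planned contrasts for each outcome: (a) PFP follow-up minus baseline, for hypothesis 1, and (b) the between-group difference in change, for hypothesis 2. Estimate both from the mixed model already planned. Report the mean difference, 95% confidence interval and Cohen's d for every outcome, whatever the omnibus p-values. Keep the Bonferroni correction for the remaining exploratory pairs.

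The cost is a sentence or two in the plan and longer results tables. More contrasts will be tested without an omnibus screen, which should be acknowledged when the results are read. No new data are needed, and the article describes participants as still being followed up, so the change can be made before the follow-up results are analysed.
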